## Abstract

**Background::**

Chronic insomnia (CI) can lead to cognitive dysfunction and bring great pain to patients’ life. There is no effective intervention for cognitive dysfunction caused by CI. Shenmen (HT7) is the first choice for insomnia treatment. However, the effect and mechanism of this acupoint on cognitive function after insomnia is not clear. Therefore, the purpose of this study is to explore whether magnetic stimulation of HT7 can improve cognitive impairment of CI by regulating prefrontal lobe and its mechanism.

**Methods/Design::**

This is a randomized controlled clinical trial. Seventy-two subjects aged 18 to 65 years old with primary insomnia and more than 3 months were randomly divided into 2 groups according to the ratio of 1:1, and 36 healthy controls were included. The control group was given sleep hygiene and cognitive therapy in behavioral cognitive therapy technology, while the experimental group was given the behavioral cognitive therapy technology intervention and magnetic stimulation of HT7 acupoint for 30 times (2 times / d, 5 times / wk for 20 days), while the healthy control group had no intervention measures. Before treatment and 20 days after treatment, we evaluated the working memory (1-back test), episodic memory (Complex Figure Test), and problem-solving ability (Hanoi tower test) processed by prefrontal lobe to explore the effect of magnetic stimulation on cognitive function of CI and its possible mechanism. At the same time, insomnia severity index was used to evaluate sleep state, Becker depression scale was used to evaluate depression, and Beck anxiety scale was used to evaluate anxiety. Chi-squared test or rank sum test was used to collect the data of patients. If *P* value is less than or equal to .05, the difference will be considered statistically significant.

**Conclusion::**

This study explored the effect and mechanism of magnetic stimulation of Shenmen (HT7) on cognitive function of CI, and confirmed that magnetic stimulation of HT7 can be used as an alternative therapy to improve cognitive impairment of CI.

**Trial Registration number::**

ChiCTR2000034280

## Introduction

1

Chronic insomnia (CI) is a common disease in adults.^[1]^ Long term sleep disorders not only affect the quality of life of patients, but also cause cognitive impairment. Sleep deficiency can cause damage in many cognitive fields such as attention, memory, executive power, emotional control, language fluency, mental motor speed, etc.^[2]^ The worse sleep quality, the more and more areas and degree of cognitive impairment.^[3]^

At present, the cognitive impairment of CI lacks effective intervention measures, and behavioral cognitive therapy (CBT-I) lacks sufficient clinical evidence to improve the cognitive function of CI.^[4]^ Oral hypnotics may aggravate cognitive impairment.^[5]^ The possible mechanism of cognitive impairment in insomnia is increased cortical excitability^[2]^ and decreased slow wave sleep.^[6]^ Repetitive transcranial magnetic stimulation (rTMS) is a noninvasive neuromodulation technique, which is widely used in clinical practice by reducing the cortical excitability of CI patients.^[7]^ However, the use of rTMS in patients with intracranial metal implants, stents, glaucoma, and hypertension is limited.

Acupuncture and moxibustion is one of the common therapies for insomnia in traditional Chinese medicine (TCM). Shenmen (HT7) is the original point of hand Shaoyin heart meridian, which has the effect of calming and calming the mind. It is the preferred acupoint in TCM treatment of insomnia.^[8]^ The clinical effective rate of Shenmen single point in treating primary insomnia is 76.67%.^[9]^ However, it is difficult to copy the manipulation of acupuncture and moxibustion treatment, and some patients can not bear the pain of acupuncture.

Repetitive magnetic stimulation (rMS) acupoint has the similar effect as acupuncture and moxibustion, and has the advantages of quantifiable, non-invasive, and pain free.^[10]^ Compared with rTMS, rMS has fewer contraindications, so the use of rMS to stimulate acupoints to improve CI symptoms has attracted the attention of clinical workers. In clinical evidence, low frequency (1 Hz) rMS of HT7 point can make brain activity orderly and reduce brain excitability to health.^[11]^ Moreover, low frequency (1 Hz) stimulation of HT7, PC6, and SP6 by rMS can enhance the interaction between brain regions, improve the transmission speed and efficiency between brain networks, and improve the cognitive function of brain.^[12]^ However, it is not clear whether magnetic stimulation of HT7 can improve cognitive impairment associated with CI. Therefore, we designed this experiment to explore the short-term efficacy and possible mechanism of rMs stimulating HT7 on cognitive impairment of CI.

## Methods/design

2

### Study design

2.1

This is a randomized, parallel controlled clinical trial. A total of 108 volunteers were recruited. Seventy-two patients with CI were randomly divided into 2 groups, the ratio was 1:1. Both groups were given basic treatment (sleep hygiene + cognitive therapy in CBT-I Technology), and the experimental group was added magnetic stimulation of HT7 points on the basis of basic treatment. There were 36 healthy people in the control group. There was no intervention in the healthy control group.

The whole study period was 20 days. The clinical efficacy was evaluated by clinical efficacy scale and related software on the day of enrollment and the 20th day of treatment.

The clinical trial results will be reported according to the Standards for Reporting

Interventions in Clinical Trials of Acupuncture statement.^[13]^

### Ethics

2.2

This study has passed the ethics committee Shaanxi Provincial Hospital of traditional Chinese medicine ((2020) Lun Shen No. (17)), and registered on June 30, 2020 at http://www.chictr.org.cn/index.aspx, ID is ChiCTR2000034280. Informed consent has included all the subjects involved. Any modification of the study protocol or informed consent, which may affect the rights and interests of the participants or the implementation of the study, should be reported to the Ethics Committee for approval again. If there are any serious adverse events in the trial, the ethics committee should review it in time and put forward written suggestions for modification, including sufficient power to suspend the trial.

### Study population

2.3

#### Inclusion criteria of control group and experimental group

2.3.1

1.Patients aged 18 to 45 years, including 18 and 45, with no gender limit;2.Patients who meet the DSM-5 diagnostic criteria for CI;3.Patients with insomnia severity index > 7;4.Chinese handedness scale > = 7 patients;5.Patients who sign informed consent.

#### Inclusion criteria of healthy control group

2.3.2

1.Age: 18 to 45 years old;2.BMI: 18.5 to 23.9 kg/m^2^;3.Education: secondary school or above (including secondary school);4.Chinese handedness scale >= 7 patients;5.mini mental state examination>27 minute;6.patient health questionnaire-9<5 minute;7.generalized anxiety disorder-7<5 minute;8.insomnia severity index < 7 minute.

#### Exclusion criteria of control group and experimental group

2.3.3

1.Patients with insomnia accompanied by other mental diseases (depression, anxiety, fine score, double equal), physical diseases (pain, stroke, coronary heart disease, tumor, etc);2.Patients with severe depression and anxiety (patient health questionnaire-9 depression screening >= 20; generalized anxiety disorder-7 anxiety screening >= 19);3.Patients with insomnia caused by shift work, time difference, and other reasons;4.Patients with high risk of sleep apnea (the patients with more than 3 items of stop Bang questionnaire were judged as high risk);5.Patients with severe or unstable chronic diseases that are not well controlled;6.Patients with central nervous system diseases, such as epilepsy, brain tumor, hemangioma, encephalitis, acute brain injury, etc;7.Patients with metal foreign bodies within 30 cm of the treatment site;8.Patients who received transcranial magnetic stimulation (TMS), transcranial direct current stimulation, acupuncture and benzodiazepines regularly within 2 weeks before enrollment;9.Patients who depend on or abuse alcohol, drugs, and other substances.

#### Exclusion criteria of healthy control group

2.3.4

1.History of mental illness;2.Family history of mental illness;3.History of major trauma;4.Nervous system diseases (such as: cerebral thrombosis, cerebral infarction, epilepsy, brain tumor, peripheral neuropathy, etc);5.History of head trauma (e.g., coma, vomiting, amnesia, convulsions, or emergency treatment);6.Have bad habits such as smoking and drinking;7.Serious diseases of important organs (such as heart, lung, liver, kidney, etc).

#### Withdrawal criteria

2.3.5

1.Violation of inclusion criteria and clinical trial protocol or exclusion criteria;2.Less than 30 sessions of RMS treatment were performed within 20 days;3.Serious adverse events occurred;4.Lost follow-up;5.Withdrawal of consent by subject or legal representative;6.Increase the treatment that may affect the study without the permission of the investigator.

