#### Experimental group

2.7.1

The rTMS therapeutic instrument (CCY-II, Wuhan yiruide medical products New Technology Co., Ltd., Wuhan) was used. According to the theory of traditional Chinese medicine, magnetic stimulation of left HT7 point was selected. After the preparation, the stimulation coil will be placed on the left HT7 acupoint (anteromedial wrist, radial to ulnar flexor tendon, on the metacarpal wrist fold) (Fig. 1). The setting parameters are: CTBS mode, total pulse number 1800,^[14]^ stimulation intensity 15%.^[15]^ Course of treatment: twice a day, with an interval of more than 4 hours, 5 days / wk, a total of 30 treatments.

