#### Control group

2.7.2

The control group was only given basic treatment.

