### Adverse events observation

2.8

Local skin numbness around HT7 point may be related to rMS of HT7 point. During the study, a patient treatment log will be established to monitor all adverse reactions during treatment and follow-up, and appropriate intervention will be carried out.

Patients with severe insomnia during the study were given dexzopiclone (3 mg QN). However, subjects who could not tolerate 80% of the rMS intensity and / or took more than twice a week of dexzopiclone were considered withdrawn.

In case of serious adverse reactions during the treatment, report to the principal investigator immediately, record the details in the patient treatment log and take corresponding treatment measures. If the subject or researcher thinks that the patient cannot tolerate these adverse reactions, the trial can be terminated and the subject will withdraw from the study.

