### Estimation of sample size

2.11

The sample size was the minimum number of 30 cases in clinical trials. Considering the loss rate of 20%, 36 cases of N1 = N2 = 72 cases were selected in this study, and 36 cases of healthy controls were included.

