### Statistical analysis

2.13

According to the situation of data collection, data analysis will be based on the principle of intention to treat analysis and / or per protocol analysis. We will also evaluate the group effect by comparing the analysis results of the above 2 data sets to evaluate the accuracy of our analysis results.

All data will be analyzed by third-party statisticians using SPSS 23.0 (v23.0, SPSS Inc, Chicago, IL). *P* < .05 was significant. Descriptive statistics will be carried out by group and time for average, standard deviation, maximum value, minimum value, and so on.

The data in accordance with the protocol set were selected for analysis. If the data obey normal distribution, they can be described by means, and standard deviation. If the variance is uniform, the analysis of variance of complete random design can be used to compare the effect indexes. If the variance is not uniform, the rank sum test of multi group comparison of complete random design can be used. If the data does not obey normal distribution, it can be described by median and interquartile distance. The hypothesis test used the bilateral test uniformly, with *P* < .05 as the statistical significance.

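### A 30-of-30 session withdrawal rule that only the rMS arm can fail, with intention-to-treat left optional, lets patients leave one arm of the randomised comparison

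*Protocol article*

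**What the plan says.** All references are to the protocol article.

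- **Section 2.3.5 (Withdrawal criteria), item 2:** a patient is withdrawn if "Less than 30 sessions of RMS treatment were performed within 20 days".
- **Section 2.7.1 (Experimental group):** the course is "twice a day, with an interval of more than 4 hours, 5 days / wk, a total of 30 treatments".
- **Section 2.7.2 (Control group):** "The control group was only given basic treatment". There is no sham stimulation, and section 2.12 describes the trial as open.
- **Section 2.8 (Adverse events observation):** "subjects who could not tolerate 80% of the rMS intensity and / or took more than twice a week of dexzopiclone were considered withdrawn".
- **Section 2.11 (Estimation of sample size):** 30 per group is raised to 36 for a 20% loss, so 72 patients are randomised.
- **Section 2.13 (Statistical analysis):** the choice of analysis set begins "According to the situation of data collection, data analysis will be based on the principle of intention to treat analysis and / or" and ends with per-protocol analysis as the alternative. The section then adds "We will also evaluate the group effect by comparing the analysis results of the above 2 data sets". The paragraph that sets out the tests opens with "The data in accordance with the protocol set were selected for analysis".

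**The concern.** Exclusions made after randomisation are safest when they cannot depend on the assigned arm. This one does. An experimental patient who misses a single session, whether through side effects, poor response, travel or low motivation, meets a withdrawal criterion. A control patient with the same traits faces no session count at all.

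If such patients also leave the analysis, the comparison is between selected experimental patients and unselected controls. Baseline and prognostic balance is then no longer protected by randomisation. The bias could favour or disfavour rMS, depending on how non-completers differ from completers.

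An intention-to-treat analysis would guard against this, but section 2.13 leaves it open whether that analysis decides the result, or is run at all. The choice is tied to how the data turn out, in an open trial.

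**Working it through.** **1. The threshold.** Planned sessions: 30 (section 2.7.1). Minimum to avoid withdrawal: 30 (section 2.3.5). Tolerance: 30 − 30 = 0 sessions. A patient with 29/30 = 96.7% of the course is withdrawn.

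**2. Who can fail it.** Read literally, item 2 would withdraw every control, since each has zero rMS sessions. That cannot be intended, so the rule applies to the experimental arm only. In section 2.8 the intensity part is likewise one-armed. The dexzopiclone part can apply to both arms, as can items 1 and 3 to 6 of section 2.3.5.

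**3. Whether the analysis plan repairs it.** The statements in section 2.13 do not agree:
- intention-to-treat and/or per-protocol, according to data collection: intention-to-treat may not be run;
- results of the two sets compared: both are run;
- protocol-set data selected for analysis: per-protocol carries the tests.

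Section 2.13.1, on the primary outcomes, names no other set. Nothing in the article says that withdrawn patients are still assessed on day 20.

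**4. The plan's own loss figure.** 30 × 1.2 = 36, which reproduces the stated size. (Dividing instead, 30/0.8 = 37.5, gives 38.) The plan therefore allows 6 losses in 36, or 16.7% of an arm.

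**5. Size of the shift.** Let q be the share of the experimental arm removed and d the completer minus non-completer difference in SD. The whole-arm mean is (1 − q) × completer mean + q × non-completer mean, so the completer mean differs from it by q × d. The document gives neither q nor d; both are assumed.

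| Removed | q | d = 0.25 | d = 0.5 | d = 1.0 |
|---|---|---|---|---|
| 1 of 36 | 0.028 | 0.007 | 0.014 | 0.028 |
| 6 of 36 | 0.167 | 0.042 | 0.083 | 0.167 |

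Standard error of the difference with 30 v 36 patients: √(1/30 + 1/36) = 0.247 SD. The largest shift shown is 0.167/0.247 = 0.68 of a standard error.

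**6. How often the rule might bite.** The article gives no attendance rate. If sessions are missed independently with attendance p, the chance of completing 30 of 30 is p^30.

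| Assumed p | p^30 | Expected completers of 36 |
|---|---|---|
| 0.995 | 86.0% | 31.0 |
| 0.99 | 74.0% | 26.6 |
| 0.98 | 54.5% | 19.6 |

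Keeping this loss alone within 20% needs p of at least 0.8^(1/30) = 0.9926. If misses come as whole days, the chance is p^15: 0.99 gives 31.0 completers and 0.98 gives 26.6.

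The 20-day limit adds to this. If treatment runs Monday to Friday (assumed), 15 treatment days span 19 calendar days from a Monday start but 21 from any other weekday. Perfect attendance could then still miss the limit.

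**7. Effect on the test.** With no treatment effect, 36 patients per arm and a two-sided t test at 0.05, one-armed removal of a share L whose outcomes are worse by g SD was simulated (10,000 runs each). Rejection rates were 0.064 (L = 0.2, g = 0.5), 0.092 (0.2, 0.8), 0.091 (0.3, 0.5) and 0.138 (0.3, 0.8). L and g are again assumptions.

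**The case against.** The best defence is that withdrawal from treatment or study is not the same as exclusion from analysis. Section 2.3.5 never says withdrawn patients are dropped from the analysis. Section 2.13 names intention-to-treat first and promises to compare both sets, which presupposes that both are run. The protocol-set sentence may describe only the per-protocol run. The ranking of analysis sets is often left to a statistical analysis plan, and the article calls the trial a pilot. Non-adherent controls can also be removed under item 1 of section 2.3.5, for protocol violation. Finally, the figures rest on assumed inputs, the illustration assigns every planned loss to one rule, and each shift shown is below one standard error.

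Some of this stands. The bias does need the withdrawal rule and the protocol-set analysis together, its size is not known, and the promised comparison is a real, if partial, safeguard. The rest does not remove the problem. The article itself fixes the zero-tolerance rule, the data-dependent choice and the protocol-set selection, so this is stated content and not detail left for later. A general protocol-violation clause is not the equivalent of a zero-tolerance session count. The comparison of sets helps only if intention-to-treat is run and day-20 data exist for withdrawn patients. The pilot label sits beside a stated intention to confirm that the treatment can serve as an alternative therapy.

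**Conclusion.** The concern holds. The plan contains a post-randomisation exclusion with a tolerance of zero in one arm and no counterpart in the other, and its analysis section does not ensure that the primary comparison keeps those patients. The structural point needs no assumptions. The size does: 0.04 to 0.17 SD in either direction if 6 of 36 are removed and completers differ by 0.25 to 1.0 SD, and 0.01 to 0.03 SD if only one is removed. That ranges from negligible to about two-thirds of a standard error. It should be fixed: it touches the primary comparison and is cheap to correct, but the illustrated shifts do not support a more severe rating.

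**What to change.** - **Sections 2.3.5 and 2.8:** delete session count and rMS intensity tolerance as grounds for withdrawal from the study. Patients may stop or reduce stimulation; record sessions and intensity as adherence.
- **Follow-up:** collect the already planned day-20 outcomes in every randomised patient who has not withdrawn consent.
- **Section 2.13:** replace the and/or wording and the protocol-set sentence. The primary analysis includes all 72 randomised patients by assigned arm, with a stated rule for those who have no day-20 data. Per-protocol is a sensitivity analysis with a pre-stated minimum session count. For illustration, a minimum of 24 of 30 would retain 99.9% of the experimental arm at an assumed per-session attendance of 0.95, against 21.5% under the present rule.

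**Cost:** a text amendment needing ethics approval under section 2.2, and day-20 assessments in patients who would otherwise have been withdrawn. No extra patients are needed. The estimate will include patients with incomplete courses and may be diluted by an amount that cannot be predicted from the document.

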### Study settings and recruitments

2.4

This study will be carried out in Shaanxi Provincial Hospital of traditional Chinese medicine.CI subjects were mainly recruited from the wards and outpatient departments of Shaanxi Provincial Hospital of traditional Chinese medicine. At the same time, posters, leaflets, and routine free examinations will also help the recruitment of volunteers. In addition, the recruitment announcement on the official website of the hospital, official account of WeChat, micro-blog and other Internet media will help the volunteers to successfully recruit.

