### Randomization

2.12

This study is a randomized controlled open trial. The method of randomization and allocation concealment is to generate 72 serial numbers according to the order of visit. The first group was randomly assigned to the first group, and the second group was randomly assigned to the last group. The randomized grouping scheme was kept in a sealed envelope, and the envelopes were opened in turn according to the order of admission, and the grouping of patients was determined according to the allocation scheme in the envelope.

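### Withdrawal for added treatment turns on the permission of an investigator who knows the arm, and the analysis text does not secure an intention-to-treat comparison that would keep those patients in

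*Protocol article*

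**What the plan says.** Four statements in the protocol article bear on this.

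- **Section 2.3.5, Withdrawal criteria, item 6.** A ground for withdrawal is: "Increase the treatment that may affect the study without the permission of the investigator". The test has two parts: the treatment could affect the study, and the investigator did not permit it.
- **Section 2.12, Randomization.** "This study is a randomized controlled open trial". Section 2.7.2 gives the control group the basic treatment only, so there is no sham and the arm is visible.
- **Section 2.13, Statistical analysis.** Depending on how data collection goes, "data analysis will be based on the principle of intention to treat analysis and / or per protocol analysis". The next sentence says that the results from the two data sets will be compared. Two paragraphs on, before the tests are described, it says: "The data in accordance with the protocol set were selected for analysis".
- **Section 2.8, Adverse events observation.** The rescue hypnotic has a fixed limit that involves no permission: patients who "took more than twice a week of dexzopiclone were considered withdrawn".

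**The concern.** The randomised question is whether magnetic stimulation at HT7 adds anything to basic treatment. Patients who seek further treatment during the 20 days are plausibly those doing worse. Under criterion 6, two patients who add the same treatment can be handled differently: one withdrawn, one kept. The difference lies in a decision taken after randomisation by someone who knows the allocation.

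If withdrawal means leaving the protocol set, and that set carries the main comparison, the decision affects who is analysed. Should permission be given more readily in one arm, that arm keeps its poorer responders while the other loses them. The contrast is then biased, in either direction according to which arm is treated more leniently. An intention-to-treat analysis with day-20 data on everyone removes this selection, so it matters whether the plan commits to one.

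**Working it through.** **Step 1. The texts side by side.**

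| Question | Source | Answer |
|---|---|---|
| What triggers withdrawal for added treatment? | 2.3.5, item 6 | Absence of permission, not the treatment alone |
| Is the decision masked? | 2.12, 2.7.2 | No: open trial, no sham |
| Which set is analysed? | 2.13 | Intention to treat and/or per protocol; then the protocol set is selected |
| Are the two sets compared? | 2.13 | Yes, as an intention; it needs both analyses to be done |
| Is any added treatment governed by a fixed rule? | 2.8 | Yes, dexzopiclone; the discretion concerns other additions |

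One link is inferred. The article does not define the protocol set, so a withdrawn patient may be outside it, but this is not stated.

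**Step 2. The plan's own figure.** Section 2.11 starts from 30 per arm and allows 20% loss: 30 × 1.20 = 36, as stated. The allowance is 36 − 30 = 6 patients per arm. It is used below only as an upper value for the number withdrawn.

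**Step 3. Illustration A: the worst patients removed from one arm only.** Assumptions, none of them in the documents: no true effect; outcome SD 1; the k patients lowest on some score are withdrawn from one arm, while their counterparts in the other arm are permitted and kept; the score correlates r with the outcome.

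Shift in the contrast = r × (expected rise in an arm's mean when the k lowest of 36 standard-normal values are removed). By simulation (400,000 samples) that rise is 0.061 SD for k = 1, 0.160 for k = 3 and 0.291 for k = 6. The rejection rates are for a two-sided rank-sum test at 0.05 (8,000 simulations per cell; about 0.048 with nobody removed).

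| k | Shift in SD, r = 0.3 / 0.5 / 1.0 | Rejection rate, r = 0.3 / 0.5 / 1.0 |
|---|---|---|
| 1 | 0.018 / 0.030 / 0.061 | 0.048 / 0.051 / 0.060 |
| 3 | 0.048 / 0.080 / 0.160 | 0.052 / 0.063 / 0.105 |
| 6 | 0.087 / 0.146 / 0.291 | 0.063 / 0.089 / 0.223 |

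For scale, the standard error of the difference with 30 versus 36 patients is √(1/30 + 1/36) = 0.247 SD, so the largest shift is 0.291 / 0.247 ≈ 1.2 standard errors.

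**Step 4. Illustration B: permission rates that differ by arm.** Assume that a share f of each arm adds treatment and scores d SD worse, and that only those with permission (probability p) stay in the set.

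- Mean of the retained arm: m(p) = −d·f·p / (1 − f + f·p)
- Retained number: n(p) = 36 × (1 − f + f·p)
- Bias: b = m(p_E) − m(p_C), with E the experimental and C the control arm
- SE = √(1/n_E + 1/n_C)
- Type I error = 1 − Φ(1.96 − b/SE) + Φ(−1.96 − b/SE)

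Worked case, f = 0.3, d = 1, p_E = 0.2, p_C = 0.8: m_E = −0.06/0.76 = −0.079; m_C = −0.24/0.94 = −0.255; b = 0.176 SD; n = 27.4 and 33.8; type I error 0.105.

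| Permission, E vs C | Bias in SD: f = 0.1, d = 0.5 to f = 0.3, d = 1 | Type I error |
|---|---|---|
| Equal (50% vs 50%) | 0 | 0.050 |
| 20% vs 80% | 0.03 to 0.18 | 0.052 to 0.105 |
| 0% vs 100% | 0.05 to 0.30 | 0.055 to 0.211 |

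With equal permission rates and the same mix of patients there is no bias. The harm needs a difference by arm.

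**The case against.** The case on the other side is substantial.

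- **The two data sets are to be compared.** Section 2.13 says so directly, and a gap between intention to treat and per protocol is what would expose this selection. This stands as mitigation. It is incomplete, because the and/or wording allows one analysis alone, and because intention to treat helps only if withdrawn patients are still measured on day 20.
- **Criterion 6 is ordinary wording against unauthorised co-treatment.** It authorises nothing. Lists of permitted treatments and the definition of the protocol set are commonly left to a fuller document, so their absence here is no fault. What remains is what the article does state: permission as the deciding test, an open trial, and selection of the protocol set.
- **Other rules narrow the scope.** Item 1 of section 2.3.5 withdraws for protocol violations, and dexzopiclone is capped. Both are correct, and the point is confined to other additions.
- **The root lies in the choice of analysis set.** With a per-protocol comparison in front, every withdrawal rule allows selection after randomisation; the rule on fewer than 30 stimulation sessions can sensibly apply only to the experimental arm. This also stands, and it is why the remedy below acts mainly on section 2.13.

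A reader might go further and infer that investigators will permit treatment more freely in one arm, or that acupuncture will be the route, since recruitment is at a hospital of traditional Chinese medicine. The documents support neither. They give no permission rates and no frequency of added treatment. The exclusion of "Patients who received transcranial magnetic stimulation (TMS), transcranial direct current stimulation, acupuncture and benzodiazepines regularly within 2 weeks before enrollment" concerns the period before enrolment and says nothing about what would be permitted later.

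**Conclusion.** The point holds in a limited form. Withdrawal for added treatment depends on a judgement made with the arm known, and section 2.13 does not secure an analysis that is immune to it. The judgement may therefore remove patients from the main comparison differently by arm.

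It would be too strong to say that criterion 6 by itself biases the trial or that intention to treat has been abandoned. The step from withdrawal to exclusion is inferred, differential permission is only possible, and both analyses are named.

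The size cannot be derived from the documents, which give no rate of added treatment and no outcome SD. On the assumed inputs above, the false-positive rate stays at about 5% to 6% with one patient affected. With six affected in one arm only, it is about 6% to 9% for r of 0.3 to 0.5. The values above 20% need a perfect correlation or an all-or-nothing split of permission. The effect is probably small unless several patients in one arm are affected. The case for acting rests on how cheaply this route to bias can be closed.

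**What to change.** 1. In section 2.3.5, state that added treatment, permitted or not, does not end a patient's assessment or analysis.
2. Record every added treatment by arm in the existing treatment log and case report form, with or without permission.
3. Carry out the day-20 assessments in these patients.
4. In section 2.13, replace the and/or wording: intention to treat is the primary analysis of the two randomised arms, and per protocol is a sensitivity analysis only.
5. For the per-protocol set, classify added treatment by a prespecified rule that does not depend on permission, as section 2.8 already does for dexzopiclone.

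An outright ban on particular co-treatments is not needed for this purpose and can be left to clinical judgement or the full protocol. Intention to treat does not undo unequal co-treatment between arms, but item 2 makes it visible.

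The cost is a wording amendment, one line in existing records and a few extra day-20 assessments. The effect estimate may also be somewhat more diluted, because patients with added treatment stay in.
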